### Statistical analysis

For power and sample size calculations, the alpha value was set to 0.05. Our hypothesis is that CF will yield lower reoperation and complication rates, lower intra-operative radiation, and less intra-operative fluoroscopy time; thus, one-sided tests of proportions were used for sample size requirements calculations [47]. For all other variables, tests for non-inferiority were used with assumed means for ratio scalar and interval variables and assumed proportions for nominal variables [47].

Statistical power and sample size requirements for demonstrating clinically significant differences between the groups were calculated using minimal clinically important difference (MCID) values from the literature. Power and sample size data, including relevant assumptions for all calculations, are presented in Table 1.

We expect ≥ 80% power for reoperation rates, complication rates, severe complication rates, *Quick*DASH, SMFA, patient satisfaction, pain in motion and at rest, and ROM. However, we do not expect to achieve 80% power for analysis of grip strength, postoperative antibiotics use, secondary dislocation or nonunion rate, sick-leave time, fluoroscopy time, fluoroscopy DAP, or operation time (Table 1).

The minimal detectable differences (MDD) for various outcomes and study sizes are presented in Table 1. For some of the secondary and tertiary outcome measures, the MDD is smaller than the MCID meaning that the study is under-powered for proving non-inferiority between the groups. Early termination of the trial resulting in a smaller sample size would further reduce MDD, hampering the power of the study.

The final study groups consist of all participants that complete the follow-up and participants that withdraw but permit analysis; see the section “ Post-inclusion withdrawals and exclusions”. The study groups will be compared using the chi-squared test for categorical variables (reoperation, complication) and Student’s *t*-test for continuous variables.

Comparisons between the study groups will primarily be performed by “intention to treat” analyses. If large cross-over between study groups occurs, “as treated” analyses will be performed as well. Subgroup analysis stratified by Mayo classification, age, gender, open fracture, and high energy trauma is planned for all outcomes.

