### Sample size

The primary outcome measure of the study is reoperation rates, and the sample size is based on this metric. Reoperation rates are assumed to be 13% for CF and 27% for TBW, based on a previous study at our institution [16]. As active patient participation is not required to calculate reoperation rates, and as it will be collected in the same health-care system as the previous retrospective study, we do not expect any drop-out of participants (relative to that study) for assessment of reoperations. The sample size of each arm needed to achieve 80% power is 98; thus, we plan to recruit a total of 200 participants, yielding 81% power.

We expect all 200 participants to be available for analyses of peri-operatively recorded variables (age, sex, fracture type, fluoroscopy DAP, fluoroscopy time and operation time). For analyses of complications, the same assumption is made as for reoperations, i.e. no drop-out relative to our previous retrospective study. For all other variables collected at follow-up, we expect 170 participants to be available for statistical analysis. The expected power for all variables at different sample sizes are shown in Table 1, including all relevant assumptions made.

**Table 1 Tab1:** Statistical power and sample size requirements for study outcomes

	**Power *****n***** = 200**	**Power *****n***** = 170**	***n***** needed for 80% power**	**MDD *****n***** = 100**	**MDD**	**MDD *****n***** = 170**	**MDD**	**x̄ or proportion**	**SD**	**MCID**

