### Eligibility and exclusion

All patients presenting at Skåne University Hospital > 17 years old with a Mayo type 2a or 2b olecranon fracture will be eligible for the study. Patients living in our catchment area but who sustain an olecranon fracture outside the area will be eligible for inclusion if treated at our hospital. The exclusion criteria are:Participants unable to participate in follow-up (for example due to active substance use disorder, dementia, inability to communicate or understand the questionnaires (for example not speaking Swedish), or living in other administrative health-care region).Participants unable or unwilling to give informed written consent.Participants where non-operative treatment is indicated (for example frail patients).Participants with severe open fractures of Gustilo-Anderson type III.Participants with pathological fractures.Participants that are treated with surgery later than 14 days from the initial trauma.Participants operated by a surgeon who has not attended education on the present study and surgical methods provided by the study officials. If surgery is supervised by a surgeon that has attended the education, the participant will not be excluded.

If a participant meets any of the exclusion criteria, the study officials will exclude them from the study. An anonymous record of the number of eligible but excluded participant, including reason for exclusion, will be kept by the study officials.

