### Follow-up

After surgery, follow-up will be identical in both study groups (Table 2). Standard peri-operative care will be given at the hospital.

**Table 2 Tab2:** Time-points for follow-up and data gathering, SPIRIT-figure

Activity	− 0.5 to 0	0	0.5	1.5	3	6	12	36
Inclusion, allocation, and randomization	x							
Intervention, both arms	x							
Primary outcome measures								
Reoperation rate				x	x		x	x
Secondary outcome measures								
Complication rate				x	x		x	x
Severe complication rate				x	x		x	x
QuickDASH				x	x		x	x
Patient satisfaction				x	x		x	x
Pain at rest				x	x		x	x
Pain in motion				x	x		x	x
SMFA		x					x	
Tertiary outcome measures								
ROM, flexion			x	x	x		x	x
Grip strength			x	x	x		x	x
Post-operative antibiotics				x	x		x	x
Secondary non union^a^			(x)	(x)	(x)	x	(x)	(x)
Sick leave				x	x		x	x
Fluoroscopy time		x						
Fluoroscopy DAP		x						
Operation time		x						

^a^The secondary dislocation or nonunion rate will be assessed from a lateral elbow radiograph at 6 months or will be recorded if diagnosed at any other time-point

In addition to descriptive baseline data, operation time, fluoroscopy DAP, and fluoroscopy time will be recorded. SMFA-questionnaires will be administered and collected by The Swedish Fracture Register (SFR) by mail shortly after the trauma (recall of pre-injury status), and 12 months later, and this data will be retrieved from SFR by the study officials.

At 2 weeks post-operatively, the cast will be removed, and a physiotherapist will record grip strength and ROM. Any reoperations, complications, ROM, grip strength, and return to work will be recorded at 6 weeks, 3 months, 12 months, and 36 months at the outpatient clinic at the dept. of Orthopaedics by a physiotherapist. PROMs (except SMFA) will be recorded by the participants in REDCap at the same time points. Reoperations and complications are recorded in each patient’s medical journal and subsequently retrieved by the study officials at interim analysis points and at the end of the trial.

At 6 months, a lateral view radiograph will be assessed by researchers DW and GC for any secondary dislocation or non-union. If secondary dislocation or nonunion is confirmed at any other point during the study, it will be recorded.

Any issue requiring additional follow-up or treatment will be handled in the standard health-care system which is public and tax-financed. After 36 months, the current follow-up will end.

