### Post-inclusion withdrawals and exclusions

Participants included during the initial assessment may be excluded at any point post-inclusion if exclusion criteria are met. If consent has been given at this point, the data already recorded will be analysed. Participants may decide to voluntarily withdraw at any point, receiving standard healthcare. Upon withdrawal, participants may choose to allow previously and future health-care data to be analysed, only allow previously collected data to be analysed, or decline analysis of any such data.

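### The protocol names intention to treat, but its definition of the final study groups and its open-ended exclusions leave some randomised patients, or their later reoperations, without a clear place in the primary comparison

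*Protocol article*

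**What the plan says.** The Statistical analysis section makes two statements about who is analysed. One is the principle: "Comparisons between the study groups will primarily be performed by “intention to treat” analyses". The other is the definition of the analysed groups: "The final study groups consist of all participants that complete the follow-up and participants that withdraw but permit analysis". The second ends with a cross-reference to the section on post-inclusion withdrawals and exclusions.

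That section says: "Participants included during the initial assessment may be excluded at any point post-inclusion if exclusion criteria are met". It adds: "If consent has been given at this point, the data already recorded will be analysed". It does not mention data arising after the exclusion. Patients who withdraw get three choices: past and future data may be used, only past data, or none.

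Under Eligibility and exclusion, the study officials make the exclusions. Under Blinding, those officials know the treatment. Allocation takes place shortly before the patient enters theatre (Allocation and randomization).

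For the primary outcome, the Sample size section says that "we do not expect any drop-out of participants (relative to that study) for assessment of reoperations", because no active part is needed from the patient. The Follow-up section says that reoperations and complications are noted in the medical journal and "subsequently retrieved by the study officials at interim analysis points and at the end of the trial".

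**The concern.** Intention to treat means that every randomised patient is compared in the arm to which they were allocated. A set defined by completing follow-up or by formal withdrawal depends on events after randomisation, and so does a set from which patients can be removed at any later time. If completion or exclusion is related both to treatment and to the chance of reoperation, the arms are no longer comparable and the primary result can be biased either way. The people who decide on exclusions know the treatment, and analysing a blinded data set afterwards does not undo that.

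The loss is also avoidable. The reoperation status of a patient who stops attending can still be read from the records that the trial plans to search.

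**Working it through.** **1. Which randomised patients have a place in the analysis?**

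| Patient after randomisation | Statistical analysis | Withdrawals and exclusions | Sample size / Follow-up |
|---|---|---|---|
| Completes follow-up | Included | – | Counted, from records |
| Withdraws, permits some or all data | Included | Data used as permitted | Counted, from records |
| Withdraws, refuses all data | Not included | Not analysed | A consent matter, not a flaw |
| Dies, or stops attending without withdrawing | Not listed | Not mentioned | Counted, from records |
| Excluded later, consent given | Not listed, only cross-referenced | Recorded data analysed; later data not mentioned | Counted, from records |

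The last two rows hold the conflict. The section on the end of the trial gives three end states for a participant: completed, excluded or withdrawn. The definition of the final groups names only the first and third.

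For a patient excluded early with no reoperation so far, the protocol does not say whether the chi-squared test counts a non-event or leaves the patient out.

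**2. What does the stated power assume?**

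Inputs: 13% versus 27% (Sample size), one-sided alpha 0.05 (Statistical analysis), 1:1 allocation. Formula, with unpooled variance:

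n per arm = (z0.95 + z0.80)² × [p1(1 − p1) + p2(1 − p2)] / d²
= (1.645 + 0.842)² × (0.1131 + 0.1971) / 0.14² = 97.85, so 98.

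This reproduces the protocol's 98 per arm. Power = Φ(d / √(0.3102 / n) − 1.645):

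- 100 per arm: 80.8% (protocol: 81%)
- 85 per arm: 74.9% (Table 1 at n = 170: 75%)

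The stated figures are right. The 81% holds only if all 200 are analysed for reoperation.

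**3. How large could a bias be?**

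The protocol gives no rate of loss for reoperation, so this is illustration only. Suppose a fraction m of the TBW arm alone is lost and the lost patients have reoperation rate r. The observed TBW rate is (0.27 − m·r) / (1 − m).

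| m | r | Observed TBW rate | Difference from 13% |
|---|---|---|---|
| 5% | 50% | 25.8% | 12.8 points |
| 15% | 50% | 22.9% | 9.9 points |
| 5% | 0% | 28.4% | 15.4 points |
| 15% | 0% | 31.8% | 18.8 points |

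The true difference is 14 points, so the error can go either way. With no true difference (20% in both arms, assumed), losing 15% of one arm with a 40% reoperation rate makes that arm's observed rate (0.20 − 0.15 × 0.40) / 0.85 = 16.5%, and the two-sided type I error rises from 5% to about 9%. If losses are unrelated to reoperation, there is no bias, only lower power.

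**The case against.** The strongest defence is to read the sections together. Complete the follow-up need not mean attend every visit. Since reoperations come from the records and need no participation, a silent non-attender could be regarded as followed to 36 months. That is a reasonable reading, but the definition does not say so, it does not cover a patient who dies, and it leaves the exclusion rule untouched.

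Several stronger readings are tempting, and the defence is right to reject them:

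- *A reader might infer that only completers are analysed.* The same sentence admits withdrawers who permit analysis.
- *A reader might infer that excluded patients vanish altogether.* Their recorded data are to be analysed if they had consented. What may be lost is what happens later. Even the end of their follow-up is only implied, by the list of end states.
- *A reader might infer that the surgeon and timing criteria routinely operate after allocation.* The criterion "Participants operated by a surgeon who has not attended education on the present study and surgical methods provided by the study officials" has an exception for supervised operations, and allocation just before theatre means that surgeon and timing are normally known by then. The real gap is that the protocol sets no cut-off. The criterion on inability to take part in follow-up could arise later, though no section says it would be applied to new events, and the Discussion treats moving away as missing data.
- *A reader might infer that 15% of patients are dropped from the primary analysis.* The 170 of 200 applies to other follow-up variables, expressly not to reoperations or complications.

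The no-drop-out assumption is itself relative to the earlier retrospective study, so it does not promise complete records for everyone.

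**Conclusion.** The point holds as an inconsistency that affects who is counted for the primary outcome. The definition of the final groups omits randomised patients who die or drift away without withdrawing. The exclusion rule has no end at randomisation, is applied by unblinded officials, and secures only data recorded so far. Neither fits the stated intention to treat or the record-based count of reoperations in all 200.

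No stated figure is wrong. The size and direction of any bias cannot be derived from the protocol, and the ranges shown rest on assumed losses. The fall from 81% to 75% would occur only if the completion rule reduced the reoperation analysis to 170, which the protocol does not plan. The lower power of a two-sided test compared with the one-sided planning is a separate matter and should not be charged to the analysis set.

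**What to change.** In the Statistical analysis section, define the primary analysis set as all randomised participants in their allocated arm, except those who decline use of their data. For each withdrawer, use only what that person permits, including the option of past data only. State that reoperations and complications are taken from the records to 36 months regardless of visit attendance.

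In the section on withdrawals and exclusions, apply the exclusion criteria only up to allocation. Keep patients later found to meet a criterion in the intention-to-treat set, log them as protocol deviations, continue their record follow-up, and report their number and reasons by arm.

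Keep the planned chi-squared comparison as primary. It cannot use partial follow-up, so address death or leaving the region before 36 months in a sensitivity analysis, for example time to first reoperation with censoring.

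The cost is an amendment to two sections and a small amount of extra analysis. No visits are added, because record retrieval is already planned. Recruitment is expected to end in 2027 and follow-up in 2030, so the change can be made well before the final analysis.

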### Allocation and randomization

Prior to commencement of the study, a randomization sequence will be created by a research assistant using a tool provided by the US National Cancer Institute (NCI) [43]. The sequence will be created using maximally tolerated-imbalance (MTI) randomization and entered into the REDCap software [44, 45]. No one will be able to access the sequence once entered to into REDCap. Randomization will be stratified by age (≥ 65 years/ < 65 years), gender (male/female), and smoking (yes/no). These parameters are chosen as they are hypothesized to affect outcome and are available at inclusion.

Before the intervention, stratification data will be collected and the participant will be allocated to either intervention in the surgical ward just prior to when the patient enters the operating theatre by the steering committee using the sequence in the REDCap software, whereby a unique ID will be created for each participant.

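### The planned chi-squared test and t-test ignore the randomisation strata and the pre-injury SMFA; the cost is mild conservatism and some lost precision, and adjusting for both is cheap

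*Protocol article*

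**What the plan says.** Under Allocation and randomization, the protocol stratifies by age (65 or over against under 65), "gender (male/female), and smoking (yes/no"), which makes 2 × 2 × 2 = 8 strata. The reason given is "These parameters are chosen as they are hypothesized to affect outcome and are available at inclusion".

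Under Follow-up, SMFA questionnaires are sent by the national fracture register "by mail shortly after the trauma (recall of pre-injury status), and 12 months later". Table 2 shows the same two time points.

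Under Statistical analysis, the tests are fixed in one sentence: "The study groups will be compared using the chi-squared test for categorical variables (reoperation, complication"), and Student's t-test for continuous variables. No stratified or covariate-adjusted comparison is named. Age and gender return only in the list of subgroup analyses. Smoking does not return, and pre-injury SMFA has no stated role.

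**The concern.** Stratified allocation forces the arms to be alike on the strata, so differences between strata no longer add to the chance variation of the treatment contrast. An unstratified test still counts those differences as noise. If the strata predict outcome, its standard error is too large, its p-values are too high and its confidence intervals too wide. Subgroup analyses do not correct this, because they leave the overall comparison unadjusted.

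Pre-injury SMFA raises a different issue. It is not a stratification factor, so omitting it does not distort the t-test. It only forgoes precision that the collected data could supply for two secondary outcomes judged against a non-inferiority margin.

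The trial has little slack on its primary outcome: 98 per arm are needed and 100 are planned. Even a modest gain at no recruitment cost is therefore worth having.

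**Working it through.** **1. The protocol's own figure.** Inputs: "Reoperation rates are assumed to be 13% for CF and 27% for TBW"; "For power and sample size calculations, the alpha value was set to 0.05"; "one-sided tests of proportions were used for sample size requirements calculations". With unpooled variance:

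n per arm = (1.645 + 0.842)² × (0.13 × 0.87 + 0.27 × 0.73) / 0.14² = 97.8, so 98.

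This matches "The sample size of each arm needed to achieve 80% power is 98". The same formula gives power of 80.8% at 100 per arm and 74.9% at 85 per arm, against the stated 81% and 75%. The sample-size figure is not at fault.

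**2. Mechanism.** Let p_s be the event rate in stratum s and p̄ the overall rate. The chi-squared test uses a variance proportional to p̄(1 − p̄). With strata balanced between arms, the true variance is close to the average of p_s(1 − p_s), which is smaller by the between-stratum variance of p_s. The unadjusted standard error can therefore be too large, but not too small, for this reason.

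**3. Size and power for reoperation.** The protocol gives no prognostic strengths or stratum shares, so the following are assumptions: 50% aged 65 or over, 60% in one gender category, 15% smokers, arms balanced to within one patient in each stratum, and the same odds ratio (OR) for each factor. There were 100,000 simulated trials of 200 patients per scenario, with rates of 20% in both arms (null) or 13% against 27%. The Monte Carlo standard error is about 0.07 points for size (√(0.05 × 0.95 / 100,000)) and 0.14 points for two-sided power. CMH is the Cochran-Mantel-Haenszel test over the eight strata.

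| OR per factor | Chi-squared size, two-sided | Power, two-sided: chi-squared → CMH | Chi-squared size, one-sided | Power, one-sided: chi-squared → CMH |
|---|---|---|---|---|
| 1 | 5.1% | 71.0 → 70.6% | 5.0% | 80.8 → 80.7% |
| 1.5 | 5.0% | 71.1 → 71.2% | 5.0% | 80.9 → 81.2% |
| 2 | 4.6% | 71.4 → 72.5% | 4.7% | 81.2 → 82.1% |
| 3 | 3.9% | 71.6 → 74.8% | 4.2% | 81.7 → 83.9% |

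CMH keeps its nominal level throughout (4.9–5.1%). With unequal ORs of 4, 2 and 3 for age, gender and smoking, and 20% smokers, chi-squared has two-sided size 3.8% and power rises from about 72% to about 75.4%. On the one-sided basis the gain there is about 2.4 points (81.9 → 84.3%). A two-sided size of 3.9% corresponds to a critical value of about 2.064, so the standard error is then about 2.064 / 1.960 = 1.053 times what it should be, or roughly 5% too large.

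**4. SMFA.** Table 1 gives SD 18 and margin 9, and the Sample size section expects 170 patients, or 85 per arm. Adjusting for a baseline with correlation r to the 12-month score multiplies the standard error by √(1 − r²) and the effective sample by 1 / (1 − r²). The 95% half-width is 1.96 × 18 × √(1 − r²) × √(2/85). The values of r are assumptions.

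| r | SE factor | SE reduction | Effective sample | 95% half-width (points) |
|---|---|---|---|---|
| 0 | 1.00 | 0% | 1.00 | 5.41 |
| 0.3 | 0.954 | 5% | 1.10 | 5.16 |
| 0.5 | 0.866 | 13% | 1.33 | 4.69 |
| 0.6 | 0.800 | 20% | 1.56 | 4.33 |

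**The case against.** The strongest reply is that an unadjusted chi-squared test is a valid, slightly conservative primary analysis, and that adjustment here is an efficiency gain rather than the repair of an error. That stands, and it limits how much weight the point can bear.

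The factors may also be weak. The Discussion gives two opposing effects of age: younger patients may need more reoperations, yet better bone may reduce K-wire migration. A net age effect near zero is therefore plausible. With ORs of 1, 1.5 and 2 for age, gender and smoking, two-sided power is 70.6–71.5% for chi-squared and 70.4–71.6% for CMH across imbalance limits of 1 to 4, so the gain vanishes. At the strong end, looser balance does not remove it.

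Three stronger readings are tempting, and the protocol does not support them.

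- **That both omissions distort the error bars.** Only ignoring the strata does so, and only towards caution. Omitting pre-injury SMFA leaves the t-test valid.
- **That every patient has a pre-injury SMFA.** It is a mailed recall questionnaire. The protocol does not state that all will be returned, and recall may weaken its correlation with the 12-month score. SMFA is also secondary, with stated power of 89–94%.
- **That the true primary power is about 70%.** That figure assumes a two-sided test, which is a separate question. On the stated one-sided basis, 81% reproduces.

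A practical objection also stands. Eight strata share about 40 events (200 × 20%). With 20% smokers, a stratum such as older male smokers holds about 200 × 0.5 × 0.4 × 0.2 = 8 patients. A stratified analysis without a pre-set merging rule would leave a post hoc choice in the primary comparison.

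**Conclusion.** The point holds as a modest, near-free improvement. The protocol randomises within strata it believes prognostic and collects a baseline for SMFA, then fixes tests that use neither. No other section supplies an adjusted comparison.

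For reoperation, the consequence runs from nothing to a two-sided size of about 3.8–3.9% and about 3 points of lost power (about 2.5 one-sided). The upper end needs ORs of about 3–4 for the main factors; at 1.5 or below the effect is negligible. For the SMFA indices the cost is precision only: a standard error 5–20% larger than it need be for correlations of 0.3–0.6.

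The direction is secure. The size rests on assumed odds ratios, stratum shares, near-exact balance and correlations, none of which the protocol gives. Nothing here suggests that a positive result would be falsely positive.

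**What to change.** - **Reoperation and the other binary outcomes:** make the primary comparison a Cochran-Mantel-Haenszel test over the randomisation strata, with a stratified risk difference and 95% confidence interval. State the rule for merging sparse strata before outcome data are compared between arms.
- **Continuous outcomes:** use linear regression of the outcome on treatment and the three stratification factors. For the two SMFA indices, add the matching pre-injury score (bSMFA or dSMFA), with a simple stated rule for missing baseline questionnaires.
- **Sensitivity:** keep the unadjusted chi-squared test and t-test.

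No new variables are needed. The cost is a wording change, the two rules and slight extra analysis work. If the factors turn out not to be prognostic, the loss is under half a point of power (71.0% against 70.6% two-sided at an OR of 1). The choice should be made in advance, because adjustment chosen after seeing results would be open to challenge.

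### A Student's t-test on participants who finish follow-up ignores the earlier scores of those lost (about 15% expected), so outcome-related loss can bias the non-inferiority comparisons on repeatedly measured outcomes

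*Protocol article*

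**What the plan says.** All references are to the protocol article.

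- **Test.** Statistical analysis: "The study groups will be compared using the chi-squared test for categorical variables (reoperation, complication) and Student’s *t*-test for continuous variables".
- **Who is analysed.** The same section defines the final groups as participants who finish follow-up, plus those who withdraw but allow their data to be used. It also names intention to treat as the main principle.
- **Expected availability.** Sample size: "For all other variables collected at follow-up, we expect 170 participants to be available for statistical analysis". Reoperations and complications are exempted there, because no drop-out is expected relative to the earlier retrospective study.
- **Visits.** Follow-up schedules clinic recording at 6 weeks and 3, 12 and 36 months, and adds: "PROMs (except SMFA) will be recorded by the participants in REDCap at the same time points". Grip and range of motion are also measured at 2 weeks. SMFA has one post-operative time-point, 12 months.
- **Use of the result.** The note to Table 1 makes the MCIDs the non-inferiority margins for the analyses: 14 for QuickDASH, with SD 22. Statistical analysis adds, for sizing: "For all other variables, tests for non-inferiority were used with assumed means for ratio scalar and interval variables". The Introduction and the Null hypothesis section both expect CF to be non-inferior on these outcomes.

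**The concern.** The non-inferiority claim on function and pain is the counterweight to the hoped-for gain in reoperations. If CF halves reoperations but leaves elbows worse, these outcomes should show it.

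A two-sample t-test at a late visit uses only the scores present at that visit. A participant who scored badly at 6 weeks and 3 months and then stopped responding contributes nothing, although the trial holds those earlier scores. If participants doing badly are more likely to be lost, the observed mean in an arm is too good. When CF is truly worse, more of its participants fall in the range where loss is likely. Its mean is then flattered more than that of tension band wiring (TBW), and the difference shrinks towards the non-inferiority side. The loss mechanism does not have to differ between arms for this to occur.

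A likelihood-based repeated-measures analysis uses every recorded visit. It is valid under the weaker assumption that loss depends only on scores already seen.

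**Working it through.** **1. Size of the loss.** 1 − 170/200 = 15%, or 85 per arm remaining of 100.

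**2. The plan's own figures: is power the problem?** For pain and SMFA the margin is half an SD, and Table 1 prints 94% (n = 200), 89% (n = 170) and n = 138 for 80% power. The article states "the alpha value was set to 0.05". Two one-sided tests at 0.05 with a true difference of 0 reproduce all three. In SD units SE = √(2/n per arm), and power = 2Φ(margin/SE − 1.645) − 1:
- 100 per arm: SE = 0.1414; 0.5/0.1414 − 1.645 = 1.891; power = 94%.
- 85 per arm: SE = 0.1534; 0.5/0.1534 − 1.645 = 1.615; power = 89%.
- n per arm = 2(1.645 + 1.282)²/0.5² = 68.5, so 69, or 138 in total.

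For these outcomes the loss of numbers alone leaves power above 80%. The issue is bias. (The QuickDASH row prints the same three figures. They match a margin of 11, not the printed 14; that is a separate matter, and 14 is used below.)

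**3. From bias to false non-inferiority.** With 85 per arm and SD 22, SE = 22 × √(2/85) = 3.375. If the true difference equals the margin and the estimate is biased by B points in favour of CF, a one-sided 5% test declares non-inferiority with probability about Φ(B/3.375 − 1.645). B = 0 gives 5%.

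**4. Same loss mechanism in both arms.** Simulation with 100 per arm, four visits, a true difference of 14, and 15% lost overall at the last visit. Assumptions not in the article: within-patient correlation 0.5 or 0.7, and odds of loss multiplied by 2 or 4 (log-odds 0.7 or 1.4) per SD of worse score at the previous visit.

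| Correlation | Odds of loss per SD | Mean t-test difference | Bias B | False non-inferiority, t-test | All-visit estimate |
|---|---|---|---|---|---|
| 0.5 | ×2 | 13.70 | 0.30 | 6.0% | 4.7% |
| 0.7 | ×2 | 13.42 | 0.58 | 7.0% | 5.1% |
| 0.5 | ×4 | 13.06 | 0.94 | 8.6% | 4.6% |
| 0.7 | ×4 | 12.63 | 1.37 | 11.2% | 5.0% |

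The formula in step 3 agrees: B = 0.58 gives Φ(−1.473) = 7.0%, and B = 1.37 gives Φ(−1.239) = 10.8%. The arms lose different shares (about 18-20% CF, 11-12% TBW) only because CF is truly worse. With loss unrelated to outcome, both methods stay at about 5%.

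**5. Mechanisms that differ by arm.** Here 15% are lost by 36 months, loss depends on the previous score with log-odds 0.7 per SD, and the assumed correlation between adjacent visits is 0.5-0.8.
- Poor scorers lost in CF only: bias 0.7-1.5 points. Step 3 gives Φ(−1.438) = 7.5% to Φ(−1.201) = 11.5%; simulation gives 7-11%.
- Opposite patterns in the two arms: 10-23%.
- All-visit estimate: about 5% in both cases.

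**6. Where the better method also falls short.** Repeat step 4 with loss depending on the unseen last score itself. The t-test then gives 8-16% and the all-visit estimate 6-12%. The model reduces the bias but does not remove it.

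**The case against.** **This is a condensed article, and missing-data handling belongs in an analysis plan that is not shown.** That is fair for anything merely absent. But the article is not silent: it names the test and the group it is applied to. An unseen plan could add detail, but to cure this it would have to depart from the named test.

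**Per-visit testing is not stated.** Correct. It is inferred from the Null hypothesis section, which refers to follow-up time-points, and from the stopping rule on QuickDASH at any follow-up time-point. The 170 is also a sizing expectation, not a rule for handling missing values, and some withdrawers may allow later health-care data to be used. Such records would not ordinarily supply a QuickDASH or grip value.

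**The inflation depends on assumed mechanisms.** This stands. A reader might infer that the plan will produce false non-inferiority, or that the risk is as high as one in four or more. The documents do not support that. Nothing in them says that poor scorers leave one arm preferentially, still less that the arms show opposite patterns. A CF-only mechanism of half the strength gives about 0.6 points and 7% (correlation 0.7). At 12 months, with less cumulative loss, the CF-only case gives 0.6-1.1 points and 7-10%. All these biases are small against a margin of 14.

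**The remedy could be oversold.** A reader might also infer that a mixed model settles the matter. Step 6 shows that it does so only when loss depends on recorded scores. The gain in precision is only a few percent.

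**Conclusion.** The point holds as a conditional weakness in the analysis of some secondary and tertiary outcomes: QuickDASH, pain at rest and in motion, satisfaction, grip and range of motion. The named t-test, on a group built mainly from those who finish follow-up, leaves recorded scores unused. It thereby exposes the non-inferiority comparison to outcome-related loss.

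At the printed QuickDASH margin of 14 and a one-sided 5% level, false non-inferiority is:
- about 5% if loss is unrelated to outcome;
- roughly 6-11% if loss depends on earlier scores, by the same mechanism in both arms or in CF only (the upper end of the same-mechanism range needs the stronger dependence, odds ×4 per SD);
- about 10-23% for opposite patterns, an extreme case.

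The correlations and loss strengths are assumptions; the SD, the margin and the 15% come from the article. It would be wrong to take equal mechanisms in both arms as harmless, since they are not when CF is truly worse. It would equally be wrong to extend the point to the primary outcome. Reoperations and complications are taken from records with no relative drop-out expected, and SMFA has only one post-operative time-point.

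**What to change.** For QuickDASH, pain at rest, pain in motion, satisfaction, grip and range of motion, replace the t-test with one likelihood-based mixed model for repeated measures per outcome:

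- **Participants:** all randomised with at least one post-operative value.
- **Fixed effects:** arm, visit, arm-by-visit, and the stratification factors (age group, gender, smoking).
- **Covariance:** unstructured across visits.
- **Decision:** read the CF minus TBW difference and its confidence interval at one prespecified visit and compare it with the margin. Other visits are supportive.
- **Sensitivity analysis:** one, shifting the missing CF values by the margin in the unfavourable direction, because the model protects only against loss that depends on observed scores.

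The cost is wording only. No new data or visits are needed, and with follow-up expected to end in 2030 the change can be prespecified well before the final analysis. The downside is a slightly more complex model and a missing-at-random assumption that has to be stated.
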